**Table 2 Tab2:**
[figure not shown]
Schedule of enrollment, interventions, and assessments

### Participant timeline (Table 2) {13}

#### Sample size {14}

Our enrollment target is 350, which will allow detection of intervention effects on viral suppression at 12-month follow-up. Based on data from our preliminary studies [66] and corroborated by national estimates [32], we expect that 57% of women who are newly initiating ART and randomized to the PST condition will be virally suppressed at the 12-month follow-up. With 350 women randomized equally to both conditions, we will have 80% power with a two-tailed alpha level of 0.05 to detect differences between a proportion of 57% in the PST condition and 73% in the ImpACT + condition. This power calculation assumes we will retain 80% of participants over the study period. In the pilot, we were able to successfully retain 80% of all participants (83.3% of newly initiating participants) for the duration of the study [45].

#### Recruitment {15}

Clinic staff will refer all women who receive a positive HIV diagnosis or present themselves for care at the ARV initiation clinic to our study offices. In a private office, English and isiXhosa-speaking study staff will greet potential participants and ask if they would like to participate in a screening questionnaire. Prior to screening, study staff will administer oral consent that highlights confidentiality and enumerates the sensitive nature of the screening items. As receipt of an HIV diagnosis and disclosure of traumatic sexual experiences can both be distressing, study staff will judge whether newly diagnosed women should be screened same day or at her next clinic visit. Our window period of 2 weeks to 4 months post ART initiation allows for flexibility in recruitment based on individual participant needs.

Screening consists of three major sections: (1) oral consent for screening; (2) a questionnaire that includes six questions on demographics, three questions on interpersonal violence (IPV), four questions on sexual trauma, two questions on depression, and seven questions on traumatic stress symptoms; and (3) written consent for medical record access in order to confirm eligibility. Eligible participants will be given information about the trial and, if interested, scheduled for a baseline assessment. Participants who indicate high risk of suicide during screening will be assessed by on-site study interventionists to determine need for referral for additional mental health care. The project manager and clinical supervisor will confirm the interventionist’s assessment and determine whether the participant should be excluded.

## Assignment of interventions: allocation

### Sequence generation {16a}

1:1 allocation to either the intervention or control condition will be determined by a random number chart generated using an independent web-based online system (https://www.sealedenvelope.com). Randomization will be stratified by initiation status (naïve initiator, restarter, defaulter), clinic, and pregnancy status (pregnant, not pregnant) to ensure equal distribution of study conditions.

### Concealment mechanism {16b}

Randomized blocks of 4 and 6 will be used within the study sites to ensure that assessment staff are unaware of condition prior to allocation and to ensure balanced assignment to condition over time.

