## Assignment of interventions: blinding

### Who will be blinded {17a}

Given differences in content and number of sessions, the experimental (ImpACT +) and control (PST) providers delivering the intervention cannot be masked to participant allocation. To avoid contamination, ImpACT + and PST providers will be trained separately and receive supervision by two distinct psychologists with separate debriefing sessions throughout the trial. Research assistants will inform participants of their intervention allocation post-baseline and are therefore not blinded post randomization. An independent assessor blinded to participant condition will conduct 4-, 8-, and 12-month assessments. The independent assessor will be trained, supervised, and attend debriefing sessions separately throughout the trial. Investigators, data analysts, and outcome assessors will be masked to participant allocation, with condition revealed at the conclusion of analysis.

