## Oversight and monitoring

### Composition of the coordinating center and trial steering committee {5d}

A formal coordinating center is not needed for this single-site study.

Daily support for the trial is provided by:

Principal Investigators: provides scientific oversite and responsibility.

Clinical supervisor: supervises nonspecialists interventionists.

Clinical psychologist: emotionally supports field staff.

Project director: oversees daily trial activity and supervises control.

Senior research assistant: supervises research assistants and field data collection.

Project coordinator: organizes data collection, ensures data quality, trial registration, and annual reports.

Research assistants: take informed consent, administer assessments, and schedule appointments.

The study team meets weekly.

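### The concealment section credits blocks of 4 and 6 with concealment that blocking cannot give, and the research assistants who enrol women also learn past allocations, so they could guess the next one better than chance

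*Protocol article*

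**What the plan says.** All references are to the protocol article.

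- **Concealment mechanism {16b}** consists of one sentence, which begins: "Randomized blocks of 4 and 6 will be used within the study sites to ensure that assessment staff are unaware of condition prior to allocation". It then adds balance over time as a second purpose of the blocks.
- **Sequence generation {16a}** sets 1:1 allocation, stratified by initiation status (three levels), clinic and pregnancy status (two levels). Study setting {9} gives four clinics.
- **Implementation {16c}** says that staff at the US university create the allocation table and load it into REDCap. Study staff use the REDCap form only once baseline is complete. The woman is then told whether she has a 6-session or a 3-session intervention, and further details wait for her first session.
- **Who will be blinded {17a}**: "Research assistants will inform participants of their intervention allocation post-baseline and are therefore not blinded post randomization". The 4-, 8- and 12-month assessments are done by a blinded independent assessor.
- **Plans for assessment {18a}** has research assistants administer the baseline battery verbally.
- **The oversight section {5d}** lists their duties: "Research assistants: take informed consent, administer assessments, and schedule appointments".
- **Recruitment {15}** says that "study staff will judge whether newly diagnosed women should be screened same day or at her next clinic visit", within an enrolment window of 2 weeks to 4 months after ART initiation.

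**The concern.** The section that should say how the next assignment is hidden names a feature with the opposite tendency. Permuted blocks make each assignment depend on the earlier ones in the same sequence, so a person who knows the earlier ones gains information about the next.

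Here the role that learns the earlier ones is also the role that consents women, runs baseline and schedules appointments. Being unblinded after one woman means being informed before the next. The arms visibly differ in number of sessions, so a preference for one arm in a particular case is conceivable.

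Two things are at stake. One is who enters when, which could leave the arms unlike in prognosis. The other is how the baseline traumatic stress and coping items are asked and recorded by someone with a hunch about the arm; these are the starting values of the hypothesized mediators. Neither can be reliably detected or corrected afterwards.

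**Working it through.** **The plan's own figures.** The article gives no figure for predictability. Its sample size reproduces and is not affected by this point. With 57% vs 73%, pooled proportion 0.65, two-sided alpha 0.05 and 80% power:

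n per arm = [1.96·√(2·0.65·0.35) + 0.842·√(0.57·0.43 + 0.73·0.27)]² / 0.16² ≈ 138.3, so 139. The total is 278, and 278/0.80 = 347.5, so 348, against 350 stated.

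**Inputs for predictability.** Blocks of 4 and 6; 1:1 allocation; 3 × 4 × 2 = 24 strata; 350/24 = 14.6 women per stratum on average. Assumed, because the article does not say: the two sizes are equally likely and in random order, blocks run within strata, and the observer sees every earlier allocation in the stratum.

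**Guessing rule.** Guess the arm that is behind in the stratum, and toss a coin when the arms are level. The tally returns to zero at the end of every block, so this rule needs no knowledge of the block sizes.

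**Exact expected correct guesses per complete block.**

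- Block of 4, by position: 1/2 + 2/3 + 2/3 + 1 = 2.833, which is 2.833/4 = 70.8%.
- Block of 6, by position: 0.5 + 0.6 + 0.6 + 0.7 + 0.7 + 1 = 4.1, which is 4.1/6 = 68.3%.
- Equal mix of the two: (2.833 + 4.1)/(4 + 6) = 69.3% in a long sequence.

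**Simulation, mixed blocks of 4 and 6.**

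| Situation | Correct guesses | Certain assignments |
|---|---|---|
| 15 women per stratum, tally per stratum | about 68% | about 6% |
| Long sequence (350), tally per stratum | 69% | 5.6% |
| Clinic-level tally only (6 strata, about 88 women) | 57-58% | not computed |
| No information | 50% | 0% |

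The long-sequence result agrees with the exact 69.3%. The certainty figures do assume that the observer knows the two block sizes. For that observer the best possible guess at 15 per stratum is no better than the simple rule (67.5% vs 67.6%), so knowing the sizes adds certainty in a few cases but hardly changes the overall hit rate.

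**Where the 68% comes from.** At 15 per stratum about 58% of assignments occur when the arms are unequal. In those the guess is right (0.676 − 0.42 × 0.5)/0.58 = 0.80 of the time; in the other 42% it is a coin toss.

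**What mixing the sizes achieves.** In long sequences, fixed blocks of 4 would make 33% of assignments certain and fixed blocks of 6 would make 25% certain. Mixing cuts certainty to about 6% but leaves the hit rate near 69%.

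**A wording point that moves the figure.** Section {16b} speaks of blocks within study sites, while {16a} stratifies on three factors. If blocks ran within clinics only, a clinic tally over about 88 women would be the relevant one, and the hit rate would be about 69% rather than 57-58%.

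**The case against.** The strongest reply is that concealment is in place and merely sits under the next heading. The table is made and held away from the clinics, and REDCap releases an assignment only after consent and baseline. Nobody can look up the next arm, and no woman can be turned away after her arm is seen. This stands, and it means a reader should not infer that allocation is unconcealed.

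A reader might also infer that research assistants can predict the next assignment and so steer enrolment. The article does not support that, for four reasons.

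- About 94% of assignments remain uncertain, and the 68% needs a separate tally in each stratum. Nothing says that anyone keeps tallies, that field staff are told the block sizes, or that one research assistant sees every allocation at a clinic.
- The stated discretion is narrow: same day or next visit, for newly diagnosed women. It belongs to study staff; that research assistants share in it is an inference from their consenting and scheduling duties.
- Delay changes a woman's arm only if another woman in her stratum is randomized in between. Enrolment from February 2021 to November 2023 is about 34 months, and 34/14.6 is about 2.3 months between women in an average stratum. Larger strata fill faster, but quick steering is implausible in an average one.
- The motive and any biased baseline scoring are conjecture.

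The primary outcome is a laboratory viral load and follow-up assessors are blinded, so its measurement is not in question. Selection at entry could still affect the comparison.

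What survives the reply is that a central release prevents looking up but not guessing, and that the article puts past allocations in the hands of those who bring the next woman in.

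**Conclusion.** The point holds as a misattributed safeguard combined with an avoidable exposure. Section {16b} claims for the blocks a property that they lack. The actual mechanism is the REDCap release, and it leaves guessing open to staff who take consent, run baseline and schedule.

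The size is a hit rate of about 68% with stratum tallies and 57-58% with a clinic tally, against 50%, with about 6% of assignments certain. These figures rest on equally likely, randomly ordered block sizes, on 24 strata of average size, and on full sight of earlier allocations. They measure opportunity. No bias in the treatment effect follows from them, because that depends on whether and how often anyone acts on a guess, and the article gives no evidence that anyone does.

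It is worth acting on because providers cannot be masked, so protection against selection depends on concealment at entry.

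**What to change.** 1. **Implementation {16c} and Who will be blinded {17a}.** The research assistant only marks baseline complete in REDCap. The allocation is released to the provider team, who are unmasked in any case. The providers tell the woman her arm and book her intervention sessions. Booking has to move with the allocation: if research assistants still schedule six or three sessions, the arm is revealed again. The same applies to chasing missed sessions under {18b}.
2. **Concealment mechanism {16b}.** Replace the claim about blocks with the central REDCap release after baseline as the mechanism. Keep balance over time as the purpose of blocking, and state whether blocks run within clinics or within all 24 strata.
3. **Block sizes.** Keep them out of site-facing material. This is a minor gain, since guessing the arm that is behind does not need them. Regenerating unused lists during enrolment is not needed.

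The cost is a change of REDCap user rights and a short procedure change. The woman learns her session schedule from the provider rather than at the baseline visit, and providers take on booking. Section {16c} already leaves further details to the first session. The change helps only women enrolled after it, and some leakage may remain because ImpACT + sessions take place in study offices at the same sites.

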### Implementation {16c}

Study staff at Columbia University and Irving Medical Center will create the allocation table and upload it to REDCap. Following completion of the baseline assessment, study staff will use the Research Electronic Data Capture (REDCap) [82] randomization form to assign the participant to either ImpACT + or the PST condition. Participants will be informed that they have been assigned to either a 6-session or 3-session intervention and that they will receive further details at the first treatment session.

## Assignment of interventions: blinding

### Who will be blinded {17a}

Given differences in content and number of sessions, the experimental (ImpACT +) and control (PST) providers delivering the intervention cannot be masked to participant allocation. To avoid contamination, ImpACT + and PST providers will be trained separately and receive supervision by two distinct psychologists with separate debriefing sessions throughout the trial. Research assistants will inform participants of their intervention allocation post-baseline and are therefore not blinded post randomization. An independent assessor blinded to participant condition will conduct 4-, 8-, and 12-month assessments. The independent assessor will be trained, supervised, and attend debriefing sessions separately throughout the trial. Investigators, data analysts, and outcome assessors will be masked to participant allocation, with condition revealed at the conclusion of analysis.

### Procedure for unblinding if needed {17b}

Randomization allocation will be revealed to the statistician after finalization of the main data analysis.

## Data collection and management

### Plans for assessment and collection of outcomes {18a}

Participants will go through the full trial informed consent process at baseline, after which RAs will verbally administer a battery of psychological assessments and other self-report measures in isiXhosa. Independent assessors will administer the same battery at 4-, 8-, and 12-month follow-up assessments. Assessments will take approximately 60 min and will be conducted in a private room at the clinic. Study staff will clarify any questions and refer participants who indicate high suicide risk during the interviews to the medical officers for further assessment and referral. Blood samples to measure viral load and ARV adherence via DBS will also be collected at all follow-up assessments. Relevant HIV care data will be abstracted from participants’ medical records.

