**Methods:**

This study will be conducted in Khayelitsha, a peri-urban settlement situated near Cape Town, South Africa. Using a hybrid type 1 effectiveness-implementation design, we will randomize 350 WLH initiating ART to the ImpACT + experimental condition or the control condition (three weekly sessions of adapted problem-solving therapy) to examine the effectiveness of ImpACT + on viral suppression, ART adherence, and the degree to which mental health outcomes mediate intervention effects. ImpACT + participants will receive six once-a-week coping intervention sessions and six monthly maintenance sessions over the follow-up period. We will conduct mental health and bio-behavioral assessments at baseline, 4, 8, and 12 months, with care engagement data extracted from medical records. We will explore scalability using the Consolidated Framework for Implementation Research (CFIR).

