### Eligibility criteria {10}

The study will enroll women living with HIV engaging with care at one of the four study clinics. Women will be eligible for enrollment in the trial if they meet the following criteria: (1) Living with HIV and between 2 weeks and 4 months since initiation of first-line ART (as new initiators, restarters or defaulters); (2) history of sexual abuse or assault during childhood, adolescence, or adulthood, using four items based on the WHO CIDI [59] and the Childhood Trauma Questionnaire [60]; (3) endorsement of any PTSD symptoms as assessed by the Breslau PTSD screener [61]; (4) 18 years or older; (5) isiXhosa speaking; and (6) receiving HIV care services at a study clinic. Patients will be excluded and referred to psychiatric services if they meet criteria for high risk of suicide. Suicidal ideation and severity will be assessed using items adapted from the suicidality subscale of the Mini International Neuropsychiatric Interview [62]. Pregnant women will be eligible to enroll. Additional exclusion criteria include patients initiated on second- or third-line ART, the inability to provide informed consent, or inability to communicate in isiXhosa or English.

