### Outcomes {12}

The primary outcome measure is viral suppression at 12 months, determined by HIV viral copies per milliliter of blood. Viral suppression will be reported as a dichotomous variable with the threshold for viral suppression defined as < 50 copies/mL, as determined by the Abbott Alinity assay (Sensitivity Limit of Detection 20 copies/mL).

The following secondary outcome measures will be assessed at baseline, 4, 8, and 12-month timepoints:ART adherence:◦ Dried blood spots measuring levels of tenofovir-diphosphate (TFV-DP) (at 12 months)◦ Medical record abstraction of pharmacy visits and pharmacy refill data◦ Adapted Adult AIDS Clinical Trials Group self-report measure of adherence [74, 75]HIV care engagement (medical record abstraction):◦ Missed visits (# of monthly visits missed and binary indicator of any missed monthly visit)◦ Visit adherence (proportion of visits kept)◦ Gaps in care (whether > 90 days have elapsed between visits)◦ Visit constancy (# of 90-day intervals with > 1 completed visit).◦ Mental health mediators will be assessed by the following measures (all timepoints):Post-Traumatic Stress (PTSD Checklist-Civilian version for the DSM-5 (PCL-5) [76]Coping [45], adapted from [77–81].

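### The sections disagree on when blood is taken, and no viral load at entry is described for women up to 4 months into ART; this costs precision and interpretation but does not bias the 12-month comparison

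*Protocol article*

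**What the plan says.** Four places in the protocol article bear on this.

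- **Abstract, Methods:** "We will conduct mental health and bio-behavioral assessments at baseline, 4, 8, and 12 months".
- **Outcomes {12}:** the lead-in reads "The following secondary outcome measures will be assessed at baseline, 4, 8, and 12-month timepoints", but the first item under it is "Dried blood spots measuring levels of tenofovir-diphosphate (TFV-DP) (at 12 months"). The primary outcome is suppression below 50 copies/mL at 12 months.
- **Plans for assessment and collection of outcomes {18a}:** after baseline consent, "RAs will verbally administer a battery of psychological assessments and other self-report measures in isiXhosa". Blood appears later in the same paragraph: "Blood samples to measure viral load and ARV adherence via DBS will also be collected at all follow-up assessments". HIV care data are also to be abstracted from medical records.
- **Eligibility criteria {10}:** women must be "between 2 weeks and 4 months since initiation of first-line ART (as new initiators, restarters or defaulters").

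Randomisation follows the baseline assessment ({16c}). It is 1:1 and stratified by initiation status, clinic and pregnancy ({16a}), not by viral load or time on ART. The primary analysis ({20a}) compares 12-month suppression between arms by a modified Poisson risk ratio. Table 2, the schedule of assessments, could not be read in the copy reviewed.

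**The concern.** These statements cannot all be followed as written. If {18a} governs, no study sample precedes randomisation, although the abstract leads a reader to expect a biological measure at baseline. TFV-DP is measured either at 12 months or at every follow-up.

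The missing baseline value matters because of the entry window. A woman two weeks into treatment and one four months in may differ widely in viral load, and both can fall in the same initiation-status stratum. Suppression at entry is likely to be among the strongest predictors of suppression at 12 months. Without it, the trial cannot:

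- adjust the primary comparison for it and gain precision;
- show whether the arms were balanced on it;
- say whether ImpACT+ helped women reach suppression or keep it;
- use it among the baseline predictors of loss to follow-up on which {20c} relies.

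The 4-month sample is no substitute. The ImpACT+ sessions start within two weeks of baseline and run over two months, so that sample is taken after treatment.

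**Working it through.** **1. The plan's own figure.** Inputs from Sample size {14}: 57% against 73%, two-sided alpha 0.05, 80% power, 350 randomised, 80% retained.

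- Evaluable per arm: 175 × 0.80 = 140.
- Pooled formula: n = [1.96·√(2 × 0.65 × 0.35) + 0.8416·√(0.57 × 0.43 + 0.73 × 0.27)]² / 0.16² = (1.322 + 0.560)² / 0.0256 = 138.3, so 139 per arm.
- With dropout: 139 / 0.80 = 173.75, so 174 per arm and 348 in total, against 350 planned.
- Power at 140 per arm: Φ[(0.16·√140 − 1.322) / 0.665] = Φ(0.859) = 80.5%.

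The sample size reproduces and does not depend on an entry viral load.

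**2. Does unmeasured entry suppression bias the comparison?** This was simulated with 140 per arm, 40,000 runs per setting and a Wald test on the log risk ratio with no baseline term. Assumptions not in the documents: 20% to 60% suppressed at entry, of whom 65% to 85% are suppressed at 12 months, with the control arm fixed at 57% overall.

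| Scenario | Rejection rate | Mean difference between arms |
|---|---|---|
| No effect | 4.5% to 4.9% | about 0.000 |
| Planned effect | 80% to 81% | about 0.160 |

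There is no bias and no loss against the stated power.

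**3. What would knowing entry status be worth?** Let b be the share suppressed at entry and d the difference in 12-month suppression by entry status. Both are assumptions; the documents give neither. The share of outcome variance explained is R² = b(1−b)d² / (0.57 × 0.43), where 0.57 × 0.43 = 0.2451. The gain in effective sample size is about 1/(1−R²) − 1. The last column is the shift in the arm difference from a 1 SD chance imbalance, d·√(2b(1−b)/140).

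| b | d | R² | Gain | 1 SD shift |
|---|---|---|---|---|
| 0.15 | 0.30 | 0.0115/0.2451 = 4.7% | 4.9% | 0.043 × 0.30 = 1.3 points |
| 0.30 | 0.40 | 0.0336/0.2451 = 13.7% | 15.9% | 0.055 × 0.40 = 2.2 points |
| 0.50 | 0.40 | 0.0400/0.2451 = 16.3% | 19.5% | 0.060 × 0.40 = 2.4 points |

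Putting 140/(1−R²) = 147 to 167 per arm into the power formula of step 1 gives about 82% to 87%, against 80.5%.

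**4. Is the imbalance an extra error?** No. The standard error of the arm difference at 57% is √(2 × 0.2451/140) = 5.9 points. In the middle row (2.19/5.92)² = 0.137, which is R² itself. The imbalance is a component of the standard error already reported, and adjustment would remove it.

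**5. Sensitivity.** On the grid used in step 2, R² runs from 0.7% (20% suppressed at entry; 65% against 55% at 12 months) to 48% (60% suppressed at entry; 85% against 15%). The documents do not narrow this range.

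**The case against.** A reader might infer that blood is drawn only at follow-up, so that no woman has a viral load before randomisation. The text does not go that far. Section {18a} does not say only, Table 2 could not be read, and record abstraction, for which consent is sought under {26b}, may already supply a value. A missing entry value is the natural reading of {18a}, but it is not established.

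A reader might also infer that early suppression cannot be told apart from an intervention effect. The design rules that out. Allocation is 1:1 with a concurrent control, and the analysis compares arms at 12 months, not change from baseline. Suppression from earlier ART is expected equally in both arms, as step 2 shows.

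Other points on this side stand in part:

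- The 12-month limit on TFV-DP can be read as an exception to the lead-in. Samples could be collected at every follow-up and only the 12-month level used as the outcome. That would be coherent, but the protocol does not say it.
- Bio-behavioral is a loose term for an abstract and would be thin evidence of a contradiction by itself.
- Initiation status is a stratum and carries some of the information on entry viral load, so part of the gain in step 3 may already be available.
- A recorded viral load may predate the current ART start or a gap in treatment, and then says little about status at entry.
- Covariate choice is commonly left to the analysis plan. The finding is therefore the conflict on sampling and the need to secure the entry value, not the absence of a covariate list.

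**Conclusion.** The point holds in a limited form. The sections shown do not agree on which blood samples are taken at which visit, and none of them clearly provides an entry viral load in a population whose time on ART at entry ranges from 2 weeks to 4 months. The primary risk ratio, its type I error and the sample size are unaffected.

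If there is no entry value, the losses are precision, a balance check, the distinction between achieving and maintaining suppression, and strength in the loss-to-follow-up models. The precision loss corresponds to about 5% to 20% in effective sample size. That assumes 15% to 50% suppressed at entry, a 30 to 40 point difference at 12 months and entry status known for every woman. Under those inputs it is a ceiling for any value taken from records.

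The issue is worth correcting because the remedy is cheap and planned power has little slack. It does not threaten the validity of the trial.

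**What to change.** 1. Reconcile the abstract, Outcomes {12}, {18a} and Table 2 so that each blood measure has one stated set of visits. Give a single TFV-DP schedule, separating collection from assay if they differ.
2. State whether a viral load before randomisation exists. If one is drawn at baseline, say so in {18a} and use it as a covariate in the primary modified Poisson model.
3. If none is drawn, abstract for every woman, including those already enrolled, the last viral load dated before randomisation, its date, and the ART start date. Code the value as suppressed, not suppressed or none on record, and enter it with time since ART start in the primary model. The dates show which values predate the current ART start.

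**Cost:** protocol wording and a few more fields in an abstraction already planned, under a record review for which consent is already sought. There will be a none-on-record group, mainly naive initiators, and the gain will fall short of the range above. No new blood draw is required.
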